## Abstract

**Background:**

The Michigan Prevention Research Center, the University of Michigan Schools of Nursing, Public Health, and Medicine, and the Michigan Department of Community Health propose a multidisciplinary academic-clinical practice three-year project to increase breast cancer screening among young breast cancer survivors and their cancer-free female relatives at greatest risk for breast cancer.

**Methods/design:**

The study has three specific aims: 1) Identify and survey 3,000 young breast cancer survivors (diagnosed at 20–45 years old) regarding their breast cancer screening utilization. 2) Identify and survey survivors’ high-risk relatives regarding their breast cancer screening utilization. 3) Test two versions (Targeted vs. Enhanced Tailored) of an intervention to increase breast cancer screening among survivors and relatives. Following approval by human subjects review boards, 3,000 young breast cancer survivors will be identified through the Michigan Cancer Registry and mailed an invitation letter and a baseline survey. The baseline survey will obtain information on the survivors’: a) current breast cancer screening status and use of genetic counseling; b) perceived barriers and facilitators to screening; c) family health history. Based on the family history information provided by survivors, we will identify up to two high-risk relatives per survivor. Young breast cancer survivors will be mailed consent forms and baseline surveys to distribute to their selected high-risk relatives. Relatives’ baseline survey will obtain information on their: a) current breast cancer screening status and use of genetic counseling; and b) perceived barriers and facilitators to screening. Young breast cancer survivors and high-risk relatives will be randomized as a family unit to receive two versions of an intervention aiming to increase breast cancer screening and use of cancer genetic services. A follow-up survey will be mailed 9 months after the intervention to survivors and high-risk relatives to evaluate the efficacy of each intervention version on: a) use of breast cancer screening and genetic counseling; b) perceived barriers and facilitators to screening; c) self-efficacy in utilizing cancer genetic and screening services; d) family support related to screening; e) knowledge of breast cancer genetics; and f) satisfaction with the intervention.

**Discussion:**

The study will enhance efforts of the state of Michigan surrounding cancer prevention, control, and public health genomics.

**Trial registration:**

NCT01612338

## Background

Breast cancer is the second most common cancer among U.S. women and the second leading cause of cancer death [1]. One of the goals of the Comprehensive Cancer Control Plan for Michigan is to further “reduce the female breast cancer death rate” [2]. This study strives to contribute to this goal, specifically for female Young Breast Cancer Survivors (YBCS) diagnosed at 20–45 years old and their female relatives who may be at increased risk.

Breast cancer survivors have a 2-fold higher risk of developing a second breast cancer, compared to women without breast cancer, matched for age, breast density, and use of mammography [3]. In addition, unaffected first- and second-degree relatives of women diagnosed with breast cancer younger than 50 years of age have respectively a 2.3 and 1.5 increased relative risk for breast cancer [4]. The initial step in determining an unaffected woman’s risk for breast cancer is the collection of a thorough family history that includes first- and second-degree relatives on both the maternal and paternal sides of the family [5]. However, a review of health plan charts conducted by the Genomics Program at the Michigan Department of Community Health revealed that only 42% of charts had documented a family history of breast cancer, while, 98% of these charts did not document age of onset for the affected family members [6]. According to national recommendations, women with a strong family history of breast cancer should be referred for genetic counseling [7,8]. Yet, a phone survey of the general adult population living in Michigan revealed that only 12% of high-risk women older than 40 years of age actually received this service [6]. Furthermore, only 56% of these high-risk women had a Clinical Breast Exam (CBE) in the past 12 months; only 48% had a mammogram in the past 12 months; and, only 44% had both a mammogram and CBE in the past 12 months [6].

The study aims to increase breast cancer surveillance and early detection by targeting YBCS identified from a state cancer registry and their high risk relatives. Specific aims are to:

Aim 1: Identify and survey 3,000 female YBCS reported to the cancer registry who were diagnosed between the ages of 20–45 years and determine: (a) their current breast cancer screening status; (b) perceived barriers and facilitators to screening; (c) willingness to participate in an intervention to increase breast cancer screening; and (d) willingness to serve as a breast cancer screening advocate for their high-risk relatives.

Aim 2: Identify and survey up to two unaffected first- and/or second-degree female relatives per YBCS and determine: (a) their current breast cancer screening status; (b) perceived barriers and facilitators to screening; and (c) willingness to participate in an intervention to increase breast cancer screening. Female relatives will be between 25–64 years and have an increased risk of breast cancer based on the YBCS’ age of diagnosis.

Aim 3: Compare the efficacy of two versions of an intervention on breast cancer screening utilization and other outcomes among YBCS and their high-risk female relatives. YBCS and their high-risk female relatives will be randomly assigned as a family unit to receive either the Targeted or the Enhanced Tailored version of the intervention. (Description of the two intervention methods follows).

## Methods/design

This prospective, randomized trial involves testing the efficacy of two versions of a printed intervention (i.e., Targeted version and Enhanced Tailored version). Participants will be randomly assigned as family units (YBCS and her high-risk female relatives) to receive one of two versions. The survivor and relative(s) of enrolled family units will be mailed a self-administered baseline survey prior to receiving the intervention (Time 1). A self-administered, follow-up survey will be mailed to YBCS and high-risk relatives nine months post-intervention (Time 2).

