### Outcomes

A follow-up survey will be mailed to YBCS and their high-risk relatives nine months after the baseline survey to determine the effect of each intervention version on: a) utilization of breast cancer screening and genetic counseling; b) perceived barriers and facilitators to screening; c) self-efficacy in utilizing screening services; d) family support related to screening; e) knowledge of the genetics of breast cancer; and f) satisfaction with the intervention. Table 2 describes the concepts and variables of the study (left column), the instruments that will be used to measure these variables (middle column), and the assessment times (right column). Instruments have been previously validated with various populations (see references in Table 2). Completion of the baseline and the follow-up questionnaires takes approximately 45 min.

**Table 2 T2:** Variables, instruments and assessment times

**Concepts/variables**	**Instruments**	**Survivor**		**High-risk relative**	
		**Baseline**	**Follow up**	**Baseline**	**Follow up**

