**Behavior**					
Current screening practices	Behavioral risk factors surveillance system [24]	√	√	√	√

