### Statistical analyses

Analyses will be conducted separately for YBCS and high-risk relatives. A descriptive analysis of baseline data will provide screening utilization practices, perceived barriers and facilitators to screening, and other outcomes for YBCS and high-risk relatives. This will include tabulating counts and frequencies of variables including demographics, cancer history, screening history and perceived breast cancer risk. Bivariate analyses (using the Chi-square test for differences in proportions and *T*-test for differences in means) to assess the associations between demographic factors, clinical indications and screening practices will follow. We will stratify by using the Cochran-Mantel-Haenszel test to assess the association between family history, screening practices, genetic counseling/testing, and perceived facilitators/barriers while controlling separately for race/ethnicity, age-group, and time since diagnosis. Outcomes include both continuous and dichotomous measures. Means and standard deviations will be used to describe the results. Continuous measures taken only at post-test will be compared between the two intervention groups by simple t-tests. After assuming an autocorrelation of data r = .30, changes over time in continuous measures will be tested by paired t-tests. For dichotomous measures taken only at post-test, the rates in the two groups will be compared by logistic regression. The proportions in each group will be reported to describe the results. If a baseline version of the measure is available, logistic regression will be conducted on the post-tests with the pre-tests included as covariates. Chi-square tests will be conducted to test the changes over time. The above analyses will establish whether the groups are equivalent, determine whether post-tests differ between the two groups, and assess the significance of changes over time. To further meet Aim 3, regression analyses (linear or logistic) will be used to test which factors (beyond the intervention) predict obtaining breast cancer screening.

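### With one follow-up at nine months, women recently screened on an annual cycle cannot fall due, and the yes/no baseline covariate does not identify them; the comparison between versions is diluted, not biased

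*Protocol article*

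**What the plan says.** Aim 3 is to "Compare the efficacy of two versions of an intervention on breast cancer screening utilization and other outcomes". Screening is the first outcome named, though none is labelled primary.

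On timing, Methods/design states: "A self-administered, follow-up survey will be mailed to YBCS and high-risk relatives nine months post-intervention (Time 2". The Abstract also counts nine months from the intervention. The Outcomes section uses a different start: "A follow-up survey will be mailed to YBCS and their high-risk relatives nine months after the baseline survey".

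On measurement, the Behavior row of Table 2 lists "Current screening practices" at baseline and at follow-up for both groups, and shows no look-back period. The only period attached to screening anywhere is in the Background, where a phone survey documents the shortfall that the study hopes to reduce. For mammography it reports that "only 48% had a mammogram in the past 12 months". Over the same period the survey gives 56% for a clinical breast exam and 44% for the two tests together.

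On analysis, the Statistical analyses section treats survivors and relatives separately. A dichotomous outcome with a baseline version is compared by logistic regression on the post-test with the pre-test as covariate. For pre-post change, "Chi-square tests will be conducted to test the changes over time".

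**The concern.** Nine months is shorter than an annual cycle. A woman who had a mammogram one month before the intervention and keeps to a yearly schedule has no screen due before Time 2. Neither version can change her answer, and the article does not set her aside.

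The planned covariate does not solve this. It records whether she was screened before baseline, so it treats a woman screened one month earlier the same as one screened eleven months earlier. Only the second can fall due by Time 2.

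Two things are at stake. The difference between the versions shrinks towards zero, so a null result could partly reflect the calendar. The change-over-time test also depends on a look-back that the article does not show. If the surveys do not collect screening dates, no later analysis can recover this information.

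**Working it through.** **The plan's own sample size.** For h = 0.30, two-sided alpha 0.05 and 80% power, n = 2 × ((1.960 + 0.842)/0.30)² = 174.4 per group. The two-sample t-test gives 175.4, which rounds up to the stated 176. With 35% attrition, 352/0.65 = 541.5, the stated 542. The figures reproduce.

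**Women who cannot fall due.** Assumptions: annual screening, spread evenly over the year, and the intervention mailed at about the time of the baseline survey. Let p be the proportion screened in the past 12 months. The share screened in the last three months is f = p × 3/12.
- p = 0.44: f = 11%
- p = 0.48: f = 12%
- p = 0.56: f = 14%

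**Diluted effect.** With unchanged behaviour, the nine-month rate among women who can respond is r = (p − f)/(1 − f). At p = 0.48 this is 0.36/0.88 = 0.409. Apply h = 0.30 to these women only: q = sin²(arcsin√r + 0.15) = 0.558. Two scorings are possible:
- (a) 12-month look-back at Time 2: f + (1 − f)r against f + (1 − f)q
- (b) screened since the intervention: (1 − f)r against (1 − f)q

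Power = Φ(h√(n/2) − 1.96), with n = 176 per group:

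| p | Scoring | Rates compared | Observed h | Power |
|---|---|---|---|---|
| 0.44 | (a) | 0.440 vs 0.572 | 0.265 | 70% |
| 0.44 | (b) | 0.330 vs 0.462 | 0.271 | 72% |
| 0.48 | (a) | 0.480 vs 0.611 | 0.265 | 70% |
| 0.48 | (b) | 0.360 vs 0.491 | 0.267 | 71% |
| 0.56 | (a) | 0.560 vs 0.687 | 0.264 | 70% |
| 0.56 | (b) | 0.420 vs 0.547 | 0.256 | 67% |

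**At the numbers the article expects** (p = 0.48, before any allowance for clustering):
- Relatives: 604 × 0.65/2 = 196 per arm. Power is about 75%, against 84% at h = 0.30.
- Survivors: 1,200 × 0.65/2 = 390 per arm, or (1,200 − 100) × 0.65/2 = 357 after the estimated hereditary-syndrome exclusions. Power is about 94% to 96%.
- If the 240 survivors without eligible relatives are analysed apart, as the recruitment section says, 960 × 0.65/2 = 312 per arm remain before those exclusions. Power is about 91%.

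**Due-only comparison.** 0.88 × 176 = 155 per group at the undiluted h = 0.30 gives about 75%, against about 70% with all women included.

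**Change over time, with no change in behaviour.**
- Under (a), 48% stays 48%. The baseline window covers months −12 to 0 and the Time 2 window months −3 to 9. They share three pre-intervention months, so a real change is attenuated.
- Under (b), 48% becomes 0.75 × 48% = 36%, a false fall of 12 points (11 to 14 across the three rates).

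**The other clock.** If nine months runs from the baseline survey, each month between that survey and the mailing of the intervention removes a month of exposure. At p = 0.48 it adds 0.48/12 = 4 percentage points to the not-due share.

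**The case against.** The strongest reply is that 12 months is not the trial's standard. It is the recall period of an external survey of women older than 40, whereas participants are aged 25 to 64 and half the design concerns survivors. That is right. A reader might infer that the protocol judges its own outcome by 12 months; the article does not say so. The look-back and item wording may be in the questionnaire or the full protocol, and tailoring on screening adherence implies that some working definition exists. Nothing shows that dates are not collected. What remains is that the nine-month timing and the yes/no pre-test covariate are both stated, and on an annual cycle together they leave not-due women unidentified.

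A reader might also infer that the trial is biased or that pre-post change is bound to be false. Neither follows. Both arms share the same follow-up, so the contrast is diluted equally. The false fall arises only under since-intervention scoring, which no section adopts.

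Nor does the article support a claim that the survivor comparison is underpowered: at the planned numbers its power stays above 90%. Women overdue or never screened can respond within nine months and are counted as able to in the working. The article gives genetic counseling no annual cycle, so the point does not extend to it.

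Finally, the article calls h = 0.3 typical of screening interventions. Those effects may already include women not yet due. If so, applying 0.30 only to women who can respond counts the dilution twice, and the power loss shown is an upper estimate.

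**Conclusion.** The point holds as an inexpensive improvement to the design and analysis; it is not a flaw that invalidates the comparison. On an annual cycle with even timing, about 12% of women (11% to 14%) cannot respond on screening by Time 2, and the planned covariate does not separate them. If h = 0.30 belongs to women who can respond, the observed h is about 0.27 and power about 70% at 176 per group. Relatives are the group at risk, at about 75%; survivors have room to spare. These sizes rest on external rates and assumed timing, not on trial data.

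The effect on the change-over-time test depends on the scoring: attenuation with equal 12-month look-backs, a false fall with a since-intervention count.

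Separately, Methods/design and Outcomes start the nine months at different events and must be reconciled. Counting from the baseline survey makes the dilution worse.

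**What to change.** 1. State one start for the nine months and use it throughout.
2. Make sure both surveys record the month and year of the last mammogram and the last clinical breast exam. Add these items only if they are not already there.
3. For Aim 3, count only screening dated after the intervention was mailed.
4. Keep all randomised women in the main comparison, and replace the yes/no pre-test covariate with baseline time since last screen, including a never-screened category.
5. Report alongside it the comparison among women due before Time 2. Set due status from baseline data and the interval given in the study's own materials, so that it cannot be affected by the arm.
6. For change over time, use the same look-back at both surveys and state that the Time 2 window includes about three pre-intervention months.

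A later follow-up is not needed if dates are available.

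The cost is at most two items per survey and some analysis wording. The drawbacks are recall error in the dates and about 12% fewer women in the due-only comparison, where power at 176 per group is nevertheless about 75% against about 70%.

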### Setting

The Michigan Cancer Surveillance Program is a central cancer registry that was established by law (Act 82 of 1984) [9] to collect reports on cases for *in situ* and invasive malignancies. Between 1998 and 2007, there were 7,866 YBCSs identified in the Michigan Cancer Surveillance Program [10]. This database will be used to identify and recruit YBCS. The Michigan Department of Community Health-Genomics Program and the University of Michigan-School of Nursing will enroll participating families, implement the two versions of the intervention, and collect and analyze baseline (Time 1) and follow up (Time 2) data.

### Recruitment of YBCS and high-risk relatives

Between 1994 and 2008 there were 9,000 cases of young women with breast cancer were reported to the Michigan Cancer Registry. For the study, 3,000 women diagnosed with invasive or in –situ-breast cancer between 20 to 45 years old from 1994 to 2008 will be randomly selected from the cancer registry database. The Michigan Cancer Surveillance Program will cross-reference mortality data to exclude deceased YBCS. To increase inclusion of minority and underserved women, the sample will be stratified by race. The study will oversample YBCS who are black and living in counties with the highest mortality rates for young women with breast cancer (See Figure 1).

**Figure 1 F1:**
[figure not shown]
Age-adjusted ten-year mortality rates for breast cancer by county among women in Michigan under age 50, 2000–2009.

As shown in Figure 2, it is estimated that from the initial 3,000 YBCS, approximately 1,200 will be willing to participate (40% response rate). We estimate that approximately 20% of these YBCS (n = 240) will not have any eligible high-risk female relatives (e.g. relatives will be younger than 25 or older than 64). These YBCS will be included in the study but will be analyzed as a separate group. Based on our previous experience recruiting women with familial breast cancer and their high-risk relatives [11], we project that the remaining 960 YBCS will have approximately 1,728 eligible high-risk female relatives. This estimation is based on the assumption that we will be able to identify 1.8 first- and/or second-degree, high-risk relatives per YBCS. Based on our previous experience [11], we expect that 604 high-risk relatives will be willing to participate in the study (35% response rate). Table 1 describes inclusion and exclusion criteria for YBCS and high-risk female relatives.

**Figure 2 F2:**
[figure not shown]
**CONSORT diagram-flow of study participants.** Est. = Estimated.

**Table 1 T1:** Eligibility criteria

**Eligibility criteria for young breast cancer survivors**	**Eligibility criteria for high-risk female relatives**
• Female	• Female
• 25–64 years of age	• 25–64 years of age
• Being diagnosed with unilateral or bilateral invasive breast cancer between 20 and 45 years old	• Unaffected with any type of cancer
• Being diagnosed with unilateral or bilateral DCIS^ж^ between 20 and 45 years old	• First- or second-degree relatives of the YBCS
• Michigan resident at time of diagnosis	• US resident
• Able to read and understand English	• Able to read and understand English
• Not currently pregnant, incarcerated, or institutionalized*	• Not currently pregnant, incarcerated, or institutionalized*
	• YBCS is willing to contact

^ж^ Ductal Carcinoma In Situ.

* Women who are pregnant, incarcerated, or institutionalized at the time of the study are excluded because they may not be able to follow recommendations for breast cancer screening and genetic counseling.

Recruitment procedures will involve the following steps:

1) Obtain approval to conduct research with human subjects from the Institutional Review Boards at the University of Michigan and at the Michigan Department of Community Health, and the Scientific Advisory Board of the Michigan Cancer Registry.

2) The cancer registry will send a letter to the reporting facility and the physician of record asking if they are aware of any reason that the YBCS should not be contacted to participate in the study. The YBCS will be excluded from the study if the reporting facility or physician of record responds to this letter requesting that the YBCS not be contacted.

3) If there is no reason to exclude YBCS, the cancer registry will mail an invitation letter to the YBCS requesting her participation in the study, along with an Informed Consent form, and the self-administered baseline survey. The invitation letter and consent form will explain the study and state that if the YBCS is currently incarcerated or institutionalized, or if she is pregnant, she is not eligible to participate. The invitation letter will explain that these two conditions may interfere with a woman being able to get breast cancer screening. The invitation letter and consent form include contact information for the Director of the cancer registry and the Principal Investigator of the study, and a toll-free phone number for the Michigan Department of Community Health-Genomics Program for the YBCS to ask further questions about the study.

4) YBCS who agree to participate will return the signed consent form and the completed baseline survey to the cancer registry in a postage-paid, pre-addressed envelope. There will be up to three mailed attempts to reach non-responding YBCS. The cancer registry will not release any identifiable information to the research team until the YBCS mails back her signed consent form and her baseline survey.

5) Once an YBCS agrees to participate, her contact information and baseline survey will be released to the Michigan Department of Community Health-Genomics Program. Two board-certified genetic counselors employed by the program will review all returned surveys to ascertain YBCS eligibility. If the YBCS reports being diagnosed with a known hereditary cancer syndrome such as *BRCA1*, *BRCA2*, Lynch, *PTEN* Hamartoma Tumor, Li-Fraumeni, or Peutz-Jeghers syndromes, the genetic counselors will contact her by phone and provide additional information to raise awareness about appropriate resources and clinical care. These YBCS (estimated n = 100) will be excluded from Aim 3 of the study.

6) Based on information provided by the YBCS in the baseline survey, the genetic counselors will identify up to two high-risk relatives per YBCS. Eligible high-risk relatives will be female, first- and/or second-degree relatives, and unaffected by cancer. Identification of high-risk relatives will be according to a protocol that involves pedigree analysis. Questions that assess family history of cancer allow calculations of Gail [12] and Claus [13] risk models. YBCS will be asked how many first and second degree relatives had cancer, type of cancer, and age of onset. Then YBCS are asked to list the first and second degree relatives in the family who are cancer free, their age, and whether they are willing to contact them for the study. The combination of answers in these two sets of questions allows genetic counselors to identify eligible, high-risk relatives. As explained in the informed consent form, if necessary, the genetic counselors will contact the YBCS by phone to obtain additional family history information. Each participating YBCS will be mailed a letter asking her to contact the identified high-risk relatives and request their participation in the study. Consent forms, baseline surveys and postage-paid return envelopes will be provided to the YBCS to give to her relatives. A “Project Navigator” will be available by telephone to discuss any concerns the YBCS may have about this procedure. If an identified high-risk relative does not mail back her signed consent form and completed baseline survey within six to eight weeks, the Project Navigator will contact the YBCS to determine if an alternate high-risk relative should be selected for participation.

7) Relatives’ signed consents and completed baseline surveys will be returned to the Michigan Department of Community Health-Genomics Program. This is the first time that the research team will receive identifiable information from high-risk relatives. The genetic counselors will review relatives’ signed consent forms to further ascertain eligibility for participation. After randomization, the genetic counselors will also calculate objective breast cancer risk for the high-risk relatives who will be randomized to receive the Enhanced Tailored version of the intervention. The Gail model [12] and the Claus model [13] will be used to calculate these objective risk estimates. Using two different risk estimation models is necessary because the Gail model does not apply to women younger than 35 years of age.

8) YBCS and high-risk relatives will receive a check for $10 in the mail when they return their baseline survey and a check for $20 when they return their follow-up survey.

